### Follow-up and minimization of attrition

Since attrition reduces the effective sample size and can introduce bias, strategies shown to increase response to electronic and postal questionnaires will be employed [41,42]. Six and 12 months post-randomization, participants will be sent a letter reminding them about the study and advising them that they will receive a brief follow-up questionnaire in the next few days. A $20 supermarket voucher, delivered in advance and redeemable irrespective of further participation, will be enclosed with the letter as a token of appreciation. Supermarket vouchers have been used in trials conducted by the authors previously [28-30] and have been shown to improve response rates [42]. Participants who provide an email address receive an emailed hyperlink to a brief web-based follow-up questionnaire, while participants who do not provide an email address will receive a paper questionnaire. Up to three email/postal and SMS reminders will be sent following the initial invitation to complete the follow-up surveys. Participants who do not respond to the initial and reminder emails/postal surveys will be followed up via telephone.

### Data management

Baseline data will be collected using iPads. The data collected via the iPads will be transmitted to a password-protected server located in a secure area in the Ambulatory Care Center through a wireless router and downloaded into Microsoft Access (2010 version) daily. Research staff will log participants into the e-SBI program using a unique study number so that baseline and follow-up data can be linked. Follow-up data will be collected via a web-based follow-up questionnaire when participants provide an email address, and by post otherwise. Where follow-up data is collected electronically, the unique study number will be embedded in the hyperlink to the web-based follow-up questionnaire emailed to each participant [43]. Where follow-up data is collected by post, the unique study number will be printed on the questionnaire. Participants’ study information will be linked with health-care utilization data collected by the health service using their Medical Record Number (MRN), which is a unique patient identifier for public hospitals in the Hunter New England Local Health District. Double data entry in Microsoft Access (2010 version) will be undertaken for data collected by post.

### Sample size

The estimate relates to the first co-primary outcome and is based on findings from a pilot study conducted in the same setting in 2010. The mean number of standard drinks consumed by outpatients who participated in the pilot study was 20 (SD = 15). Assuming a 5% level of significance and 80% power, we would require 289 participants per group (578 total) at six months to detect a difference of 3.5 standard drinks (35 g ethanol) per week (18%) between the groups, as found by [name] et al. [29] and similar to the 38 g ethanol reduction found in the meta-analysis by Kaner et al. [3]. Assuming 25% attrition at six months post-randomization, which is conservative given that attrition was 15% at 12 months in a study utilizing similar methods conducted by [name] and colleagues [29], 772 participants will be randomized at baseline.

### Statistical methods

The first co-primary outcome (number of standard drinks consumed in the past week at six months post-randomization) and the secondary outcome, also related to number of standard drinks, will be analyzed with negative binomial regression. Similarly, number of inpatient, outpatient, and emergency-department presentations will be analyzed using negative binomial regression. The secondary outcome of number of drinking days in the past week will be analyzed using logistic regression within a generalized estimating equation framework to take into account the repeated measurements on individuals. Each individual’s data will be entered as the binomial outcome of yes/no to drinking on each day. The proportions meeting guidelines will also be analyzed using logistic regression. The AUDIT score will be analyzed using linear regression. All analyses will control for baseline AUDIT-C score [44] as in previous trials reported by the investigators [29]. Participants will be analyzed in the group to which they were randomized (intention-to-treat). Sensitivity analyses using pattern mixture models will be conducted to explore the potential impact of any missing follow-up data [45,46]. Additional analyses will be conducted to determine whether the intervention was more efficacious among (1) patients with a lower AUDIT-C score; (2) patients in the intervention group who requested that a copy of their electronic personalized feedback be sent to them; (3) younger people; (4) men; and (5) patients who reside in a relatively advantaged postal area [47].

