**Methods/Design:**

This randomized controlled trial will be conducted in the outpatient department of a large tertiary referral hospital in Newcastle (population 540,000), Australia. Some 772 adults with appointments at a broad range of medical and surgical outpatient clinics who score 5–9 inclusive on the Alcohol Use Disorders Identification Test-Consumption (AUDIT-C) subscale will be randomly assigned in a 1:1 ratio to electronic alcohol screening alone (control) or to e-SBI. As randomization will be effected by computer, researchers and participants (who will be invited to participate in a study of alcohol use over time) will be blinded to group assignment. The primary analysis will be based on the intention-to-treat principle and compare weekly volume (grams of alcohol) and the full AUDIT score with a six-month reference period between the groups six months post randomization. Secondary outcomes, assessed six and 12 months after randomization, will include drinking frequency, typical occasion quantity, proportion who report binge drinking, proportion who report heavy drinking, and health-care utilization.

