### Screening

Research staff will log eligible consenting outpatients into the e-SBI program on an iPad using a unique study number. Page 1 of the e-SBI will describe the *Hospital Outpatient Alcohol Project* (HOAP). Page 2 will collect demographic data (gender, age, and postcode) and contact information (email address). Page 3 will ask respondents if they have consumed alcohol in the last 12 months (yes/no). Those who respond “no” will be excluded at this point. Page 4 will ask respondents if they are receiving treatment for alcohol-related problems (yes/no). Those who respond “yes” will be excluded at this point. Page 5 will comprise the three alcohol consumption questions from the Alcohol Use Disorders Identification Test (AUDIT) [21]. These questions comprise the validated three-item screening tool known as the AUDIT-C [22], which has specificity and sensitivity similar to the full 10-item AUDIT. The AUDIT-C will be used to screen outpatients for hazardous and harmful alcohol consumption because completion of the full AUDIT has been shown to produce reductions in self-reported alcohol consumption [23]. Upon clicking the continue button on this page, AUDIT-C scores will be calculated (range 0–12 with higher scores reflecting more severe drinking problems). Participants who score less than 5 will be excluded at this point. A minimum score of 5 points was selected because it has high specificity while maintaining good sensitivity for identifying patients with hazardous or harmful drinking [22]. Participants who score more than 9 will also be excluded at this point because the probability of alcohol dependence with an AUDIT-C score above 9 is high [24], and these patients probably require more than brief intervention [25]. Participants in the control group will not be asked other questions about alcohol consumption at baseline, because answering questions on drinking in brief intervention trials appears to alter subsequent self-reported behavior [26].

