### Allocation and blinding

Participants will be randomly assigned (simple randomization with 1:1 allocation, no blocking, no stratification) to one of two treatment groups: electronic alcohol screening alone (control group) or electronic alcohol screening plus further assessment and personalized feedback via an iPad (intervention group). Allocation concealment will be ensured as the random assignment will be computer-generated (SecureRandom.random_number method in Ruby [27]) and effected immediately following screening via a hand-held device (iPad). Participants will be blind to the true nature of the study, as they will be asked to consent to participate in a series of surveys on alcohol use among outpatients and will not be aware that they have been randomized. Data analysts will be blinded to group allocation when they prepare and clean the data. Only after the data has been locked will unblinding occur and the analysis be completed. No other blinding is required as there are no care providers (the intervention is delivered via iPads), and there are no outcome assessors (the study outcomes are self-reported by blinded participants).

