### Intervention

The intervention will be informed by a decade of research by [name] and colleagues [28-31] and will comprise two parts: (1) additional assessment using an iPad and (2) electronic personalized feedback, including normative feedback which has been shown to reduce alcohol consumption in heavy drinking university students [32] and adult problem drinkers [33].

The assessment questions will comprise (1) the remaining six questions of the AUDIT [21]; (2) a question regarding the largest number of standard drinks (in Australia, this refers to a drink containing 10 g alcohol) consumed on a single occasion in the last four weeks; (3) a question regarding the duration of the drinking episode in hours; (4) body weight (for the purpose of estimating peak blood alcohol concentration [BAC]); and (5) the Leeds Dependence Questionnaire (LDQ) [34].

The electronic personalized feedback will comprise (1) the participant’s AUDIT score and guidance on its meaning [21]; (2) an estimated BAC for their heaviest drinking episode in the previous month with information on the behavioral and physiological sequelae of their BAC, along with traffic-crash relative risk if they reported consuming alcohol in the past 4 weeks; (3) an estimate of their spending on alcohol in the past year; (4) a bar graph comparing their typical episodic consumption with medical recommendations [35] and that of adults of the same age and gender [36]; (5) a bar graph comparing weekly consumption with medical recommendations [35] and that of adults of the same age and gender [36]; and (6) an LDQ score with an explanation of the associated health risk [34]. It is important to note that normative feedback via the bar charts will be suppressed when participants’ episodic or weekly consumption is consistent with medical recommendations [35]. In addition to the electronic personalized feedback, three pages offering facts about alcohol (for example, the health consequences of unhealthy alcohol consumption), tips for reducing the risk of alcohol-related harm and sources of support for drinking problems (for example, contact details for services available in the local health district) will be included. The time to complete the intervention and read the electronic personalized feedback is expected to be less than 10 minutes [37]. A copy of the electronic personalized feedback will be emailed or posted to participants who agree to this information being sent to them.

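### The main models name only the truncated AUDIT-C total as a covariate, although its three items, gender and age are held in both arms before randomisation: efficiency forgone at almost no cost

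*Protocol article*

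**What the plan says.** Statistical methods (protocol article) sets negative binomial regression for weekly drinks and linear regression for the AUDIT score, the two co-primary outcomes. For adjustment it states: "All analyses will control for baseline AUDIT-C score". The reason given is consistency with the investigators' earlier trials. Age, gender, AUDIT-C score and postal area also appear in that section, as factors in the additional analyses of who benefits more.

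The Abstract admits people who "score 5–9 inclusive on the Alcohol Use Disorders Identification Test-Consumption (AUDIT-C) subscale". Screening describes the untruncated scale as "range 0–12 with higher scores reflecting more severe drinking problems".

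Screening also lists what is collected from everyone: "Page 2 will collect demographic data (gender, age, and postcode" and, three pages later, "Page 5 will comprise the three alcohol consumption questions from the Alcohol Use Disorders Identification Test (AUDIT". It adds that controls are asked nothing more about drinking at baseline. Allocation and blinding places randomisation straight after screening and describes it as "simple randomization with 1:1 allocation, no blocking, no stratification".

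**The concern.** A covariate in a randomised comparison earns its place by predicting the outcome. The AUDIT-C total is limited in two ways here. Eligibility cuts its range from 13 possible values to five, which usually weakens its correlation with anything else. It also adds three consumption answers together, so people with the same total can have reached it through different answers.

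The separate answers are the only baseline drinking information common to both arms. Gender and age are held as well, and the plan itself treats them as relevant to drinking: the feedback described under Intervention compares participants with adults of the same age and gender. Since randomisation is simple and unstratified, chance differences in these factors are addressed in the main models only as far as the AUDIT-C total captures them.

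What is at stake is precision. Outcome variance that these variables could explain stays in the error term, and the confidence intervals are wider than the data in hand require.

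**Working it through.** **1. Reproduce the plan's figure.** Inputs from Sample size: difference 3.5 drinks, SD 15, 5% significance (taken as two-sided), 80% power, 25% attrition.

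- n per group = 2 × (1.960 + 0.842)² × 15² / 3.5² = 288.4, rounded up to 289. This matches the plan.
- Power at 289 = Φ(3.5 / (15 × √(2/289)) − 1.96) = Φ(2.805 − 1.96) = 80.1%.
- Randomised: 289 / 0.75 = 385.3, so 386 per arm and 772 in total. This matches the plan.

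The calculation contains no covariate term. The nominal 80% therefore does not depend on which covariates are used.

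**2. Effect of a covariate set.** If covariates explain a share R² of outcome variance, the residual SD is 15 × √(1 − R²), and

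Power = Φ(3.5 / (15 × √(1 − R²) × √(2/289)) − 1.96).

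The equivalent gain in participants from enlarging the set is (1 − R² base) / (1 − R² full) − 1.

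**3. Numbers.** The documents give no R², so all values are assumptions. With the AUDIT-C total at R² = 0.10, power is 84.1%. Adding the items, gender and age gives:

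| Extra R² | Full R² | Power at 289 per group | Gain in effective sample |
|---|---|---|---|
| 0.02 | 0.12 | 84.9% | 0.90/0.88 − 1 = 2.3% |
| 0.05 | 0.15 | 86.0% | 0.90/0.85 − 1 = 5.9% |
| 0.10 | 0.20 | 88.0% | 0.90/0.80 − 1 = 12.5% |
| 0.15 | 0.25 | 90.0% | 0.90/0.75 − 1 = 20.0% |

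On 578 analysed participants, 2.3% to 20% corresponds to about 13 to 116 more people.

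**4. Sensitivity to the base value.** Over the same range of extra R², a base of 0.05 moves power from 82.1% to 82.9–88.0% (gain 2–19%). A base of 0.20 moves it from 88.0% to 88.8–93.6% (gain 3–23%).

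**5. Is the range of extra R² reasonable?** An illustrative simulation drew negative binomial outcomes with mean 20 and SD about 15 among people with totals of 5–9. It assumed a mapping from the item answers to weekly volume. Replacing the total by the items moved R² from about 0.05 to 0.08 when baseline volume predicted follow-up weakly, from about 0.13 to 0.21 when moderately, and from about 0.32 to 0.50 when strongly. Gender and age were not modelled. Because the outcome was generated from a frequency-by-quantity product, the exercise favours the items by construction. It shows only that the assumed range is attainable.

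The power formula is for a difference in means. It is an approximation to the planned negative binomial model, and it says nothing numerical about the AUDIT score, for which the plan gives no variance.

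**The case against.** The strongest reply is that nothing here is wrong. The plan prespecifies a sensible baseline drinking measure and gives a reason for it. It omits no stratification factor, because there is none, and it reaches its power without help from any covariate. The text does not say that no other covariate will be used, and a separate analysis plan could add some. The size of the gain rests wholly on assumed values and could be negligible. All of this stands. It makes the point an improvement and not the correction of an error. Still, the article does more than stay silent on adjustment: it states the covariate for all analyses, and on that statement the richer set is not in the main models.

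Several stronger readings are tempting, and the documents do not support them.

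- *The variables are unused.* Age and gender serve the effect-modification analyses, and the items enter every model through their sum. They are absent only as separate covariates in the main models.
- *Chance imbalance biases the result.* Randomisation leaves the estimate unbiased in expectation, and the standard error already allows for chance imbalance.
- *With 25% attrition, the analysis is valid only if dropout depends on AUDIT-C and arm alone.* Dropout may also depend on factors unrelated to the outcome given the model, and the plan commits to pattern-mixture sensitivity analyses.
- *A baseline version of the primary outcome is available.* The outcome is a seven-day diary, while Screening mentions only three consumption questions. Intervention promises "a bar graph comparing weekly consumption with medical recommendations" without listing a weekly-volume question, which suggests that the items carry volume information. But that list may be inexact: it counts six remaining AUDIT questions, where a 10-item scale with three already asked leaves seven. The items can be called a proxy and no more.
- *The gain extends to every outcome.* In the logistic models, added covariates change the conditional odds ratio being estimated, so extra precision cannot simply be assumed there. For the AUDIT score, AUDIT-C is already a natural baseline measure, so the case is weaker.

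**Conclusion.** The point holds as a low-cost gain in efficiency for the two co-primary models. The named covariate is a five-valued total, and finer baseline information collected in both arms before randomisation is left out of those models. There is no bias and no power shortfall, since the stated sample gives 80.1% power with no covariate credit.

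For weekly drinks, if the total explains 10% of variance and the added variables a further 2 to 15 percentage points, power rises from about 84% to between 85% and 90%, equal to about 2–20% more participants. Both figures for explained variance are assumptions. The lower end of the range is close to no gain, and the documents cannot say where in the range the trial would fall.

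**What to change.** Before unblinding, prespecify the following for the two co-primary models (negative binomial for weekly drinks, linear for AUDIT score):

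- the three AUDIT-C items entered separately, or a frequency-by-quantity index built from them as a proxy for baseline volume;
- gender;
- age as a continuous variable.

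If the three items are entered as linear terms, they replace the total, because they sum to it and the model could not estimate both. The commitment to control for AUDIT-C is still met. If an index is used, the total can stay beside it. Keep the AUDIT-C-only model as a sensitivity analysis for comparability with the earlier trials.

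The logistic secondary analyses can stay as planned, which avoids changing their conditional odds ratios.

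The cost is a few sentences in the analysis plan and a few parameters. With linear items, gender and age there are five covariate terms in place of one, so four more against 578 expected participants. No new data are needed. The timing matters, because covariates added after unblinding could look chosen for their effect on the result.

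### One of the five planned efficacy subgroups is self-selected after randomization and exists only in the intervention arm, so any extra efficacy found in it cannot be separated from self-selection

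*Protocol article*

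**What the plan says.** The Statistical methods section of the protocol article announces five further analyses with one common purpose: "Additional analyses will be conducted to determine whether the intervention was more efficacious among" the groups then listed. Item (2) is "patients in the intervention group who requested that a copy of their electronic personalized feedback be sent to them". The other items are lower AUDIT-C score, younger age, male sex and residence in a relatively advantaged postal area.

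The Intervention section explains how group (2) arises: "A copy of the electronic personalized feedback will be emailed or posted to participants who agree to this information being sent to them". Under Allocation and blinding, the computer randomizes straight after screening. Only the intervention arm then goes on to further assessment and personalized feedback; the control arm has screening alone. The Screening section adds that "Participants in the control group will not be asked other questions about alcohol consumption at baseline".

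Two general rules in the Statistical methods section also bear on the point. "All analyses will control for baseline AUDIT-C score", and participants are analysed by intention to treat.

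**The concern.** To say that an intervention works better in one group than in another is to make a statement about effect modification. It needs the randomized difference between arms inside the group, the same difference outside it, and a comparison of the two. Four of the listed groups allow this. Item (2) does not: its definition is limited in words to one arm, and membership depends on a choice that the participant makes after allocation.

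What is at stake is a pre-specified analysis that could be reported as evidence of greater efficacy in people who ask for a copy of their feedback, when the design cannot tell that apart from a difference in the kind of person who asks. The article lists the item beside four valid subgroups and attaches no caveat to it.

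**Working it through.** **Step 1. Can controls be classified?**

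| Subgroup | Where recorded | Before randomization? | Known in both arms? |
|---|---|---|---|
| Lower AUDIT-C | Screening, Page 5 | Yes | Yes |
| Younger people | Screening, Page 2 (age) | Yes | Yes |
| Men | Screening, Page 2 (gender) | Yes | Yes |
| Advantaged postal area | Screening, Page 2 (postcode) | Yes | Yes |
| Requested a feedback copy | Intervention section | No | No, intervention arm only |

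In a model with terms for arm, requester and arm × requester, no control has a value for requester. The interaction is not estimable. Two simple contrasts remain: requesters against all controls, which drops part of one randomized arm, and requesters against non-requesters, which contains no randomized comparison.

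**Step 2. The plan's own figures, as a scale.** The Sample size section gives SD 15, target difference 3.5 standard drinks/week, 5% significance and 80% power. The sidedness is not stated; two-sided reproduces the result.

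- n per arm = 2 × (1.960 + 0.842)² × 15² / 3.5² = 288.3, rounded up to 289, as stated.
- 289 / 0.75 = 385.3, rounded up to 386 per arm, or 772 in total, as stated.

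These figures are not in dispute.

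**Step 3. Bias with a true effect of zero.** Two quantities are assumptions, because the article gives neither:
- q, the share of the intervention arm that requests a copy;
- d, the amount by which requesters would drink less than non-requesters in any case, after adjustment for baseline AUDIT-C.

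Let requesters have mean m. Non-requesters then have mean m + d. With no effect, randomization makes the control mean equal to the whole-arm mean, q·m + (1 − q)(m + d) = m + (1 − q)d. So:
- requesters against non-requesters: apparent benefit d;
- requesters against all controls: apparent benefit (1 − q)d;
- non-requesters against all controls: apparent harm qd.

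Setting the last two side by side gives (1 − q)d + qd = d. Using the same controls twice is therefore only the within-arm contrast again.

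**Step 4. Numbers.** Take d as 0.1 to 0.3 SD: 0.1 × 15 = 1.5 and 0.3 × 15 = 4.5 drinks/week.

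| Contrast | Apparent benefit (drinks/week) | Share of 3.5 |
|---|---|---|
| Within the arm, any q | 1.5 to 4.5 | 43% to 129% |
| Against all controls, q = 0.50 | 0.75 to 2.25 | 21% to 64% |
| Against all controls, q = 0.75 | 0.38 to 1.13 | 11% to 32% |

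If d is negative, every entry changes sign.

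**Step 5. Chance of a significant result with no effect.** This uses a two-sided 5% z-test with SD 15 and 289 analysed per arm, as a simple stand-in for the planned negative binomial model. For q = 0.50 and d = 3.5:
- against all controls: SE = 15 × √(1/144.5 + 1/289) = 1.53, bias 1.75, rejection rate 21%;
- within the arm: SE = 15 × √(1/144.5 + 1/144.5) = 1.76, bias 3.5, rejection rate 51%.

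At q = 0.50 the rates are 10% and 21% for d = 2, and 37% and 81% for d = 5. With d = 0 both are the nominal 5%.

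**The case against.** **The article names a question but no contrast or model.** That detail is commonly left to an analysis plan, which is not shown here, and principal-stratification methods can in principle estimate an effect in would-be requesters. This stands in part: the naive contrasts are inferred, not stated. But more detail about an ordinary subgroup analysis would not supply the missing control counterpart. Only a different question, or a causal method with strong assumptions of its own, could do so, and the article signals neither.

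**Baseline AUDIT-C is controlled for.** It may absorb part of the prognostic gap, which is why d above is defined as the residual gap. It does not capture motivation or concern about drinking, and by design controls answer no other alcohol questions at baseline.

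**Stronger readings.** Three are tempting, and the article does not support them.
- A reader might infer that participants decide after seeing their feedback, so that the request is a reaction to it. The Intervention section does not say when in the iPad session they are asked. Only that the request follows randomization is supported, and that is enough for the defect.
- A reader might infer that the analysis will show greater efficacy in requesters even if the intervention does nothing. Requesters could instead be heavier or more worried drinkers, which would bias the result the other way, and the copy itself may have a real effect.
- A reader might take 43% to 129% of the target as the size of the bias in general. It applies to the within-arm contrast only and rests on an assumed gap.

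**Conclusion.** The point holds: item (2) cannot answer the question set for it. The group is self-selected after randomization, exists in one arm only and has no identifiable control counterpart, so a finding of extra efficacy could not be told apart from self-selection. This follows from the article's own text and needs no numerical assumption.

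The size of the problem is unknown. The illustrative figures rest on assumed values of the residual gap and the request share, on a true effect of zero and on the pilot SD of 15, which is not described as adjusted. They show that a modest gap could be comparable with the target effect, not that it will be.

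Severity is moderate to low. This is one of five additional analyses, and the article does not say that any conclusion will rest on it. The co-primary intention-to-treat comparisons, the other four subgroups and the sample size of 772 are unaffected.

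**What to change.** Remove item (2) from the list of efficacy subgroups. Report the number, baseline characteristics and outcomes of requesters descriptively, labelled as a non-randomized association within the intervention arm, with no claim of differential efficacy. This costs a change of wording and needs no new data or participants.

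If an effect in would-be requesters is truly wanted, the plan should name a causal method, such as principal stratification with baseline predictors of requesting, and state its assumptions. A question put to everyone before randomization about receiving study information would be a weak substitute. Wanting general information is not the same as asking for one's own alcohol feedback, and the question could hint at the purpose of a study whose participants are meant to be unaware that they are randomized.
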